### **Using ActiMyo outside the Institute of Myology**

The patient will leave the Institute of Myology, taking the Actimyo device (a sensor placed on the wrist and the otherone placed on the wheelchair). Beforehand he will receive a full explanation of its functioning. At the end of the day, Actimyo will be removed from the wrist and will be connected to USB port of patient's PC for charging. The next day, before starting his usual activities, Actimyo will be fasten to the wrist by the patient himself or by someone from his family. The new recording begins automatically. The box fastened to the wheelchair will be switched on (in the morning) and off (at the end of the day) by pressing a button. The patient will have a little diary that will be given to him where he will be able to write down the time and the date of the

beginning and the end of an activity (like brushing his teeth, eating, using the computer, getting dressed (see Appendix 1).

## **10. DATA COLLECTION**

The evaluations will be conducted by a physiotherapist, a psychomotor therapist or a trained medical doctor. An information form will be used to write down the results of the tests mentioned above. In addition, an examiner will write down the passive movements (induced by a doctor or a parent) during an assessment day.

## **11. EXPECTED PROFIT**

Profit is not expected out of the patient participating in this protocol.

## **12. DURATION OF THE EXCLUSION**

The exclusion period is not expected after the inclusion of patients. Neither extended follow-up, nor persistent effect are expected.

## **13. MANAGEMENT OF WITHDRAWAL FROM A TRIAL**

Subjects who do not want to follow the protocol for one reason or another can leave the trial without justification. They will be replaced by another person of similar age. The patients who do not succeed to realize one or more tasks can continue the protocol.

## **14. MANAGEMENT OF ADVERSE EFFECTS**

There are no serious predictable adverse effects for this study given that the clinical tests take place in controlled and reliable environment, and given that these tests present any risk. All the tests are not invasive and do not have any serious side effect. The risks associated with this study, are connected to the realization of forced movements (fatigue, muscular pains, cramps). The muscular evaluations will be stopped in case of appearance of pain or cramp.

All the adverse effects, that is to say all the symptoms, clinical signs, reactions that will develop or will aggravate during the study, will be immediately written in the space provided for

this purpose in the experimental form and the principal investigator as well as to the sponsor informed. The adverse effects will be declared within 48 hours to the sponsor. The evolution of each effect will be followed until recovery, stabilization, or until it is clearly established by mutual agreement that the effect is not related to the current study.

During the use of the device at home, all the adverse effects will be indicated to the medical investigator. A phone number as well as an e-mail address will be given to the patient and to his parents for any question relative to the functioning of the device or for indicating any technical problem.

## **15. COMPENSATION**

The participation in the present protocol is free and does not give any compensation. Nevertheless, the traveling expenses of the patients and their legal parents / representatives will be paid off by the promoter on basis of presentation of the original documentary evidences (transport according to the choice: train, taxi, VSL.) or of a fixed 0.32-euro / km allowance in case of the use of a vehicle.

Meal expenses of the patients and their accompanying person will be paid off a maximum of 15-euro per person.

## **16. INVESTIGATOR'S COMMITMENTS**

The research will be conducted in compliance with the French regulations, including dispositions related to biomedical research in the Public Health Code, Article L. 1121-1 and following, the Bioethics law, the information technology and liberties law (CNIL), the Helsinki Declaration as well as the Recommendations for Good Practice and the present protocol.

Before the implementation of the research, the coordinating investigator will put forward the project to the opinion of the Ethics Committee (CPP) Ile-de-France VI (Pitié-Salpêtrière - [name]) according to the Article L 209 of the Huriet law and will provide them with all the necessary information, the information form and the consent form or other relevant document before being presented to the Committee. The trial will only begin when the Institute of Myology has been informed of a favorable unreserved opinion issued by the CPP in regards to the protocol submitted. The promoter will inform the CPP about all the serious

or unexpected adverse effects and appearance of new facts that could presumably affect people's safety.

The investigator agrees to conduct the research according to ethical norms and regulations. He is aware that all the documents as well as all the data related to the research may be the subject of audits and inspections in respect of professional confidentiality and may not be confronted with medical secrecy. The investigator recognizes that the study results are the property of the Institute of Myology, sponsor of the research.

The Institute of Myology, as the promoter, subscribed for the entire duration of the trial to an insurance contract №. .... according to French laws and regulations on biomedical research.

## **17. INFORMATION FORM AND INFORMED CONSENT**

The written informed consent of people taking part in the research must be obtained by the investigator, members of the Order of Physicians, declared as an investigator to the sponsor before any act is performed on the basis of the research protocol, accordingly to the regulations. The consent can only be collected after reading of the information form and after the patient had the opportunity to ask all the necessary questions.

For the minor patients, the consent of the holders of the parental rights will be obtained. In the case when one of holders of the parental rights cannot attend the visit of inclusion, his/her consent will be obtained by mail before the inclusion of the patient.

According to the law of December 20th, 1988 as amended, the information given orally and in writing to patients will include information about the purpose of research, methodology and its duration, the constraints and the foreseeable risks, the opinion of the CCP, as well as the right to refuse to participate in the research or to withdraw the consent at any time without any obligation.

Patients will give their free and informed consent in writing by signing and dating the consent form. This consent form will be prepared in two copies for the patient and for the physician-investigator so that each one keeps a copy.

The investigator must ensure that the person suitable for the research will have time to make a decision freely and will be able to read and understand the information form and the consent form.

The information form of consent is a document that will be approved before the implementation of the research by the CPP, after examining the protocol.

## **18. DATA MANAGEMENT**

### **18.1. PRIVACY POLICY**

Personal data will remain confidential and anonymous.

The form for collected data will be used to register all the data. The patients will be identified by a number of the code consisted of their number of inclusion (01 for the first one, 02 for the second), the first three letters of the surname and the first two letters of the name. The informed consents will be returned to the sponsor in a sealed envelope at the end of the study.

The non-computerized data, especially written, will be archived in a secure place. The computerized data will be protected by a password.

### **18.2. DATA ANALYSIS**

#### The movements in the controlled environment

For every patient, the connection between the functional abilities (the scores) and the measured accelerations, or any other susceptible measurements to summarize the activity of the subject will be used. We will use to make a linear correlation.

The reliability of the measurements of the tests according to which each patient got the same result will be estimated according to ICC method (the correlation of intraclass correlation coefficient).

Besides, two- days' evaluation will allow assessing the ability of the program analysis to determine the passive movements (noted by one of the examiners).

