## 1. SUMMARY

The need for specifically adapted measures to assess the strength and residual function of upper limbs in non-ambulatory patients with neuromuscular diseases (particularly Duchenne muscular dystrophy and Spinal muscular atrophy) is still relevant.

Both for a regular monitoring of the clinical evaluation in non-ambulatory patients with neuromuscular diseases and for supplying with a system of quantitative measures for research, the **Pré-Acti** project proposes a continuous and homeevaluation of a complete measuring system of muscular activity in non-ambulant patients.

The principle of the measures consists in the use of the accelerometry and magneto-inertial sensors, an innovative technology invented and developed by the SYSNAV Company., for the evaluation of the linear and angular velocity

The system aims to measure the physical activity of a patient as measured by the sensors in the three dimensional space; data are recorded by the sensors attached to one of his upper limbs.

Ten non-ambulatory patients will be included and assessed at the inclusion and fourteen days later. Patients will wear a small plastic watch-like device during the evaluations and at home for fourteen days.

According to this protocol, we want to demonstrate that the simultaneous recording of linear accelerations and angular velocities in the three axes in non-ambulatory patients with myopathies can be assessed at home in a simple, reliable and reproducible manner and can evaluate the activity of upper limbs. Therefore, the purpose of **ActiMyo** is to provide a primary outcome measure that could be used in clinical trials and clinical follow-up for patients.

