#### **5. METHODOLOGY**

We plan to include 10 non-ambulatory patients with neuromuscular diseases (DMD, SMA) older than 10 years old. The non-ambulatory patients followed at the Institute of Myology and in the Pediatric Neurology department of the CHU of Amiens will be requested to participate in this study. They will be selected by Doctor [name] at the Institute of Myology and by Doctor [name] at the Hospital of Amiens.

Muscle evaluations will be conducted in the laboratory of Neuromuscular Physiology, headed by [name] at the Institute of Myology. All the tests will be conducted for neuromuscular patients during a scheduled visit to the Institute of Myology. Patients who want to participate in the study will receive a copy of the information form. The reading of it will be organized during a meeting with an investigator. Once this reading is done and the consent is signed, patients can be included in the study.

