## 8. WORKFLOW TABLE

**Table 1. Events Calendar**

|                                                              |                                    | D0         | D0–
D14 | D14        |
|--------------------------------------------------------------|------------------------------------|------------|------------|------------|
| Environment                                                  |                                    | controlled | free       | controlled |
| Collection of medical data                            |                                    | x   |            |            |
| Intercurrent events                                   |                                    |            |            | x   |
| Strength tests                                        | Hand Grip test              | x   |            | x   |
|                                                              | Pinch Test                  | x   |            | x   |
| Standardized tasks (scores)

+ ActiMyo          | Box and block test          | x   |            | x   |
|                                                              | Minnesota test (variant)           | x   |            | x   |
|                                                              | Moviplat                           | x   |            | x   |
| Tests of a daily life (scores) +
ActiMyo          | Typing a phrase on the
computer | x   |            | x   |
| Free movements

+ ActiMyo                       | Buttoning up a jacket              | x   |            | x   |
|                                                              | Having lunch                       | x   |            | x   |
|                                                              | Brushing the teeth                 | x   |            | x   |
|                                                              | Writing a phrase                   | x   |            | x   |
| ActiMyo continuously
(approximately 15h/d)

+ Diary |                                    |            | x   |            |

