## 8.2. PROGRESS OF THE EVALUATION

In the controlled environment, there are the following tests:

- Tests of strength
  - *Hand Grip* – dominant then non-dominant hand, three trials
  - *Pinch* test - dominant then non-dominant hand, three trials
- Quantified tests (with scores)

- *Box and block* test - dominant then non-dominant hand, three trials
- Minnesota test (variant) - dominant then non-dominant hand, three trials
- Moviplat - dominant then non-dominant hand, three trials
- Continuous typing a phrase on the computer: "*Les pompiers sont partis de la caserne avec leur camion rouge*" ("The fire brigade left the fire station with their red truck") - dominant hand, three tries
- Buttoning up a jacket – (device on the dominant hand), one try
- Free movements
  - Having lunch (device on the dominant hand)
  - Brush the teeth (device on the dominant hand)
  - Writing the phrase (device on the dominant hand) "*Les pompiers sont partis de la caserne avec leur camion rouge*" ("The fire brigade left the fire station with their red truck ")

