**Box and Block Test (BBT)** is a manual dexterity test, originally developed for adults with cerebral palsy (Mathiowetz et al., 1985). The test consists of a box separated on two equal compartments; one of them contains a number of wooden blocks. The patient will be asked to grab each block with one hand and put it into the empty compartment. The score corresponds the number of blocks moved to the other side during sixty seconds. The test is performed three times, alternating dominant and non-dominant limb. [Appendix 5]

**Minnesota manual dexterity test** is a standardized test, which can assess the ability of the subject to move discs for small distances. It is commonly used for the evaluation of professional competence, for the disability assessment (Gloss et al., 1982), and rehabilitation. We propose seven various wooden discs, coloured on one side, arranged in inverted "V". The patients have to turn the discs on the coloured side, starting with his dominant side, then on the uncoloured side for sixty seconds. The score corresponds the number of returned discs. Three tries will be realized alternately on each side starting with the dominant hand. [Appendix 6]

**Moviplat** is a device developed by the Institute of Myology and has been validated for DMD patients (Servais et al., 2010). The device includes two platforms. The aim is simply to touch alternately each platform. These platforms are connected to the force sensor, which directly measures the developed strength. A counter indicates the number of contacts and a chronometer

counts the time on a selected duration. The score corresponds the number of pair contacts for thirty seconds. Three tries will be realized alternately on each side starting with the dominant hand. [Appendix 7].

**Typing a sentence on the computer keyboard** is a task of daily life. We ask a subject to type with one finger of the dominant hand as many times as possible for sixty seconds the following sentence (no punctuation, no capital letters, and no corrections): "*Les pompiers sont partis de la caserne avec leur camion rouge*" ("The fire brigade left the fire station with their red truck."). The score corresponds the number of characters (including spaces) typed. The test will be done tree times.

**The buttons of the jacket:** The patient will be asked to button up a jacket, the sleeves of which have been previously strung, for sixty seconds. The score corresponds the number of buttoned buttons.

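### Read literally, the protocol's only ICC is restricted to tests whose results repeated, so it selects on agreement and does not estimate retest reliability

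*Protocol*

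**What the plan says.** The analysis of the controlled-environment tests (protocol, section 18.2) contains one sentence on reliability: "The reliability of the measurements of the tests according to which each patient got the same result will be estimated according to ICC method". It is the only ICC in the protocol. The list for the free environment that follows has comparisons within days and within the week, but no reliability coefficient.

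The data for an unrestricted analysis are collected. The summary says "Ten non-ambulatory patients will be included and assessed at the inclusion and fourteen days later", and section 8.1 repeats the same series of tests at the second visit. Section 8.2 specifies "dominant then non-dominant hand, three trials" for the strength tests, Box and Block, Minnesota and Moviplat. Typing is done three times with the dominant hand. Buttoning and the free movements are done once.

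Section 9 defines most scores as counts in a fixed time, for example "The score corresponds the number of blocks moved to the other side during sixty seconds" and "The score corresponds the number of characters (including spaces) typed" over a wide range, and "The score corresponds the number of buttoned buttons" over what is probably a short one.

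The protocol does not say whether equality of results means exact equality or equality within a tolerance, or whether it applies between trials or between visits. Nor does it say whether the ICC is for the test scores or for the ActiMyo measurements.

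**The concern.** A reliability coefficient measures how far repeated results differ within a patient compared with how far patients differ from each other. If only results that repeated are admitted, the within-patient differences that the coefficient should measure are removed, wholly or in part, before it is computed.

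This matters because the summary presents ActiMyo as a future primary outcome measure for trials. Such a trial needs the retest error in all patients, not in those whose score happened to come out the same twice. An ICC obtained under the literal rule could be carried into planning assumptions that the device does not meet.

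**Working it through.** The protocol gives no target ICC, SD or score-signal correlation, so there is no figure of its own to reproduce. The inputs from the documents are 10 patients (section 5: "We plan to include 10 non-ambulatory patients with neuromuscular diseases (DMD, SMA) older than 10 years old"), two visits, and integer count scores (section 9). The rest are assumptions, shown over a range.

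**1. ICC on the test scores.** If every retained pair has D0 score = D14 score, the within-patient variance is 0, and ICC = between / (between + 0) = 1.00, whatever the true value.

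**2. ICC on the ActiMyo measurements.** Assume a true ICC of 0.70 and total variance 1. Split each pair into its mean and its D0-D14 change:
- variance of the mean = (1 + 0.70)/2 = 0.85
- variance of the change = 2(1 - 0.70) = 0.60

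Let rho be the correlation between the change in score and the change in signal. Among pairs with no score change, the variance of the signal change is 0.60(1 - rho²). The variance of the mean is unaffected if means and changes are independent. Since ICC = [var(mean) - var(change)/4] / [var(mean) + var(change)/4], the selected ICC is

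[0.85 - 0.15(1 - rho²)] / [0.85 + 0.15(1 - rho²)]

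| rho | numerator / denominator | ICC |
|---|---|---|
| 0 | 0.700 / 1.000 | 0.70 |
| 0.3 | 0.7135 / 0.9865 | 0.72 |
| 0.5 | 0.7375 / 0.9625 | 0.77 |
| 0.6 | 0.754 / 0.946 | 0.80 |
| 0.8 | 0.796 / 0.904 | 0.88 |

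A simulation with scores rounded to integers agrees: 0.70 to 0.71 at rho 0 and 0.76 to 0.77 at rho 0.5.

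**3. How many pairs repeat exactly.** Take a normal D0-D14 difference with SD = within-patient SD × √2, and count a repeat when the absolute difference is below 0.5:

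P(equal) = 2Φ(0.5 / (SD√2)) - 1

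| Assumed within-patient SD | P(equal) | Expected out of 10 patients, one pair each |
|---|---|---|
| 0.5 (short-range score) | 0.52 | 5.2 |
| 1 (short-range score) | 0.28 | 2.8 |
| 2 | 0.14 | 1.4 |
| 3 | 0.094 | 0.9 |
| 5 | 0.056 | 0.6 |

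Pairing individual trials on two hands would give more pairs than one per patient.

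**4. What a small subset would mean.** A one-way F interval with two visits uses F = (1 + ICC)/(1 - ICC). For an observed ICC of 0.70, F = 5.67. The 95% interval is 0.20 to 0.91 with all 10 patients and -0.48 to 0.99 with 3.

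**The case against.** The strongest reply is that no restriction was intended. The document is a rough translation: section 18.2 itself names the ICC with a duplicated term, and section 14 literally says that the tests carry some risk where the sense requires none. The clause may be a garbled definition of reliability, namely the extent to which each patient obtains the same result on repetition. The summary's aim of a reproducible measure fits that. This is a fair possibility and cannot be excluded. But the clause also reads naturally as a filter, and nothing else in the protocol corrects it, so an analyst who follows the text could apply it.

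A second reply is that holding the score constant might deliberately separate device error from real change in performance. The protocol does not say so, and such an ICC would answer a narrower question than retest reliability.

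Three stronger readings are tempting, and the documents do not support them:
- *The sensor ICC is certainly biased upward.* This needs visit-to-visit changes in score and signal to correlate. Section 18.2 plans a score-acceleration correlation but gives no size and does not say that it concerns change. At rho 0 there is no inflation.
- *Almost no data would be left.* No score SD is given. The claim is plausible for typing or Box and Block but fits buttoning poorly.
- *All ten patients must repeat their result before a test qualifies.* The wording allows this, but even at 0.52 per patient the chance is 0.52^10, about 0.0014 if patients are independent, so it is implausible as a plan.

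Table 1 records "Intercurrent events" at D14. A reader might take this as a ready stability criterion, but the protocol gives it no such role. The ICC form and its confidence interval may properly be left to a statistical analysis plan and are not part of this point.

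**Conclusion.** The point holds as a defect in a stated rule. As written, the protocol's only ICC is selected on agreement, and following it would not estimate the reliability named in section 4.

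The consequence is certain only if the ICC is on scores and equality is exact: 1.00 by construction. For the ActiMyo signal it ranges from none to substantial (0.70 to 0.88 for rho from 0 to 0.8), assuming a true ICC of 0.70 and changes independent of patient means. Loss of pairs is likely to be heavy for wide-range counts and moderate for short-range ones, under assumed SDs. Whether the clause is intended or a translation slip does not alter the conclusion, because both call for the same correction.

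**What to change.** In section 18.2, delete the clause that limits the ICC to tests with equal results. State instead that the ICC for each test uses all patients measured at both D0 and D14, whatever their scores, taking the mean of the trials where three are done and the single value where the task is done once. If an equal-score ICC is wanted to isolate device error, keep it as a labelled secondary analysis with equality defined.

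The cost is one sentence and no new data or visits. The reported ICC may be lower than under the literal rule. With 10 patients its interval will still be wide, as the 0.20 to 0.91 above shows.
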